### Data collection and study follow-ups

#### Data collection procedures

Health service outcomes and patient demographic characteristics will be extracted directly from the hospital eMR. Patient-reported outcomes will be collected via an online survey, supplemented by telephone calls. At days 1, 7 and 42 following randomisation, participants will receive a text message including a link for the e-Consent Form and online survey. One reminder message will be sent to non-responders at each follow-up time point. If no response is received, a trial research officer will contact them via telephone to complete the assessment.

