##### Patient-report outcomes

Average pain intensity measured using the numeric rating scale ranging from 0 (no pain) to 10 (worst imaginable pain). This outcome will be measured at days 1, 7 and 42 following ED discharge.Quality of life measured using the EuroQol 5-Dimension 5-Level (EQ-5D-5L).^22 23^ This outcome will be measured at days 1, 7 and 42 following ED discharge.Satisfaction with ED care measured using item 31 of the ED Patient Experience of Care survey advocated by the American College of Emergency Medicine.^24^ This outcome will be measured at day 1 following ED discharge.Adverse events will be assessed on day 1 following ED discharge. Participants will complete an online survey that will include a question prompting participants to report the occurrence of any adverse event during the ED stay. Participants experiencing an adverse event will have the opportunity to include more information about the adverse event. The investigators will review the clinical notes of participants reporting adverse events and extract adverse event data. The Medical Dictionary for Regulatory Activities will be used to code adverse event data. A blinded independent assessor will review adverse event data and assign attribution to study interventions.

The trial’s schedule of assessment is presented in table 1.

**Table 1 T1:** Trial schedule of assessment

Procedures	Day 0 (emergency department visit)	Day 1	Day 7	Day 42
Patients screened for inclusion/exclusion criteria	✓			
Participants given trial flyer	✓			
Participants randomised via Research Electronic Data Capture	✓			
Interventions—physiotherapy or physician/nurse pathway	✓			
Participants invited by physiotherapist to qualitative interviews	✓			
SMS invite to online questionnaire and e-Consent		✓		
Online questionnaire completion—pain intensity, EuroQol 5-Dimension 5-Level		✓	✓	✓
Online questionnaire completion—satisfaction with care, adverse events		✓		
Completion of qualitative interviews	Patient’s interview—completed between day 1 and day 42 post emergency department discharge following randomisation.Clinician’s interview—completed after 50 patients are randomised at a participating site.			

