#### Economic evaluation

An economic evaluation, including cost-utility and cost-effectiveness analyses, of the primary-contact physiotherapy pathway compared with the physician and/or nurse practitioner pathway will be undertaken from the hospital perspective and according to the intention-to-treat principle. Data from the hospital on healthcare utilisation costs using presentation-level costing data will be collected. Intervention costs will be collected from trial records. Patient-level costing data will be calculated using the reported clinical and administrative activity received by each patient during their hospital visit. The method to collect intervention costs and the included costing data have been reported in our previous study.^27^ The effectiveness outcomes of the economic evaluation will be (1) quality-adjusted life-years (QALYs) gained over 6 weeks (cost-utility analysis) and (2) time spent in the ED avoided (cost-effectiveness analysis).

Utility-based quality of life will be measured using the EQ-5D-5L questionnaire,^22 23^ which has five domains with five levels each (mobility, self-care, usual activities, pain/discomfort and anxiety/depression), and the health utility score, which is expressed as an index value for health, will be calculated from the five domains for each participant in the trial using published Australian scoring algorithms.^28^ The score falls on the 0.0 (dead) to 1.0 (perfect health) value scale.

QALYs will be calculated using the health utility score calculated for the 6-week time point (day 42 post-trial randomisation).

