The Incremental Cost-Effectiveness Ratios (ICERs) for each effectiveness outcome expressed as additional cost per (1) QALY gained at 6 weeks (cost-utility analysis) and (2) each additional person spending at least 30 min less in the ED (cost-effectiveness analysis) will be calculated using the mean costs and the mean health outcomes in each trial arm. Uncertainty around the ICERs will be explored using a non-parametric bootstrapping analysis (5000 replications) to generate 95% CIs that will be plotted on an incremental cost-effectiveness plane. Cost-effectiveness acceptability curves will also be estimated to show the probability that the primary-contact physiotherapy pathway is cost-effective compared with the usual care group and when considering different decision maker’s willingness to pay per QALY and for each additional person spending at least 30 min less in the ED. In Australia, there is no explicit willingness to pay threshold as it depends on the decision-making context; therefore, results will be presented using a cost-effectiveness acceptability curve, illustrating the probability of cost-effectiveness across a range of willingness to pay thresholds. Costs will be expressed in Australian dollars, adjusted for inflation using the Health Consumer Price Index as published by the Australian Bureau of Statistics. We will use multiple imputation methods to address missing data for the economic evaluation as suggested by Faria *et al.*^29^

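### QALYs are defined over 6 weeks but, as worded, are computed from the day-42 utility only, which can bias the incremental QALY and the cost-utility ICER

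*Protocol article*

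**What the plan says.** The Economic evaluation section names as its first effectiveness outcome "quality-adjusted life-years (QALYs) gained over 6 weeks (cost-utility analysis"). After describing the EQ-5D-5L and its Australian scoring, it gives the QALY rule: "QALYs will be calculated using the health utility score calculated for the 6-week time point (day 42 post-trial randomisation"). The paragraph on ICERs again ties the QALY to 6 weeks and says that the ratios "will be calculated using the mean costs and the mean health outcomes in each trial arm".

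On measurement, the Patient-report outcomes section says of the EQ-5D-5L: "This outcome will be measured at days 1, 7 and 42 following ED discharge". Table 1 agrees: the row "Online questionnaire completion—pain intensity, EuroQol 5-Dimension 5-Level" is ticked at days 1, 7 and 42 and blank at day 0.

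Nowhere does the article mention an area under the curve or any use of the day-1 or day-7 utility in the QALY.

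**The concern.** A QALY over a period is utility accumulated across that period. One utility at the end of the period describes the state on that day. It equals the accumulated quantity only if utility is flat, and it gives the right difference between arms only under a particular condition on how that difference behaves over time.

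The trial enrols people with acute musculoskeletal presentations, and both pathways act on day 0. Utility can be expected to change over the following weeks, and an effect of the pathway on quality of life could well appear early. The stated rule cannot register an effect that appears at days 1 and 7 and has gone by day 42.

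At stake is the denominator of the cost-utility ICER and, through it, the bootstrap intervals and the acceptability curve per QALY. Cost-effectiveness is part of the trial's hypothesis and its third secondary objective. This is not detail left to a later plan: the article states a rule, and the rule does not deliver the outcome defined in the same section.

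**Working it through.** The documents give no utility, QALY or ICER figure, so there is nothing of the plan's own to reproduce. What can be checked is how much of the 6-week QALY the stated rule leaves out, and what that can do to the increment.

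**Inputs from the protocol.** EQ-5D-5L at days 1, 7 and 42, none at day 0; horizon 42 days. One section counts the days from ED discharge and another from randomisation; the calculation below uses nominal days.

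**Assumptions.** Linear change between measurements; the day-1 value carried back to day 0; 365.25 days per year. The protocol does not say how one utility becomes a QALY, so the stated rule is taken as u42 × 42/365.25. All utilities and arm differences below are invented for illustration.

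**Weights.** The intervals are 1, 6 and 35 days:

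QALY = [1 × u1 + 6 × (u1 + u7)/2 + 35 × (u7 + u42)/2] / 365.25 = [4 u1 + 20.5 u7 + 17.5 u42] / 365.25

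- Day 1: 4/42 = 9.5%
- Day 7: 20.5/42 = 48.8%
- Day 42: 17.5/42 = 41.7%

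Days 1 and 7 together carry 24.5/42 = 58.3%. If the first day is dropped and only days 1 to 42 are counted, the weights are 3/41 = 7.3%, 20.5/41 = 50.0% and 17.5/41 = 42.7%, and the omitted share is 23.5/41 = 57.3%. These shares depend on the visit schedule and the interpolation, not on any assumed utility.

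**When the two rules agree on the increment.** Write d1, d7 and d42 for the arm differences in utility. The stated rule minus the area under the curve is

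[42 d42 − (4 d1 + 20.5 d7 + 17.5 d42)] / 365.25 = [24.5 d42 − 4 d1 − 20.5 d7] / 365.25

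This is zero when d42 equals the weighted mean of d1 and d7, of which a constant difference is the obvious case. Otherwise it is not zero.

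**Illustrations.** Control arm 0.50, 0.65, 0.85 at days 1, 7, 42:

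| Assumed arm difference (days 1, 7, 42) | Area under the curve | Day 42 only | Effect of the stated rule |
|---|---|---|---|
| +0.05, +0.05, 0 | 1.225/365.25 = 0.0034 | 0 | gain lost, ICER undefined |
| 0, 0, +0.03 | 0.525/365.25 = 0.0014 | 1.26/365.25 = 0.0034 | 2.4 times too large |
| +0.03, +0.03, +0.03 | 1.26/365.25 = 0.0034 | 0.0034 | none |
| +0.05, +0.05, −0.01 | 1.05/365.25 = 0.0029 | −0.42/365.25 = −0.0011 | sign reversed |

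At an assumed extra cost of A$100 per patient, the second row gives A$69,571 per QALY by area under the curve and A$28,988 by the stated rule.

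**Level as distinct from difference.** For the control arm, the area under the curve is (4 × 0.50 + 20.5 × 0.65 + 17.5 × 0.85)/365.25 = 30.2/365.25 = 0.0827, against 35.7/365.25 = 0.0977 by day 42 only, which is 18% higher. That is an error in the level of one arm and does not by itself bias the difference between arms.

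**The case against.** The strongest reply is that the sentence may be loose wording for the time horizon. It does not say that day 42 is the only score used, and the outcome is defined over 6 weeks. That reading is possible but not the plain one: one score and one day are named, and no other part of the article supplies the missing step. If the intention was an area under the curve, the sentence still needs replacing.

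Three further objections stand and limit the point.

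- A reader might infer that the cost-utility result will be wrong. That does not follow: with a constant arm difference both rules give the same increment and the same ICER, and the protocol gives no utilities from which to judge how the difference will behave.
- A reader might infer that the day-1 and day-7 EQ-5D-5L data go unused. They are left out of the QALY rule only. They remain secondary outcomes, and they could inform the multiple imputation planned for the economic evaluation, whose variables are not stated.
- A reader might also see a mismatch between a 6-week QALY and costs for activity "received by each patient during their hospital visit". The documents do not establish this. The same section refers the included costing data to an earlier study that is not at hand, and the trial records 72-hour re-presentations and 30-day readmissions. Whether later contacts are costed cannot be determined from a condensed article.

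**Conclusion.** As written, the QALY rule does not measure the outcome that the same section defines. It gives no weight to days 1 and 7, which carry about 57–58% of the trapezoidal weight. Unless the between-arm utility difference is constant over the 6 weeks (more exactly, unless the day-42 difference equals the weighted mean of the earlier ones), the incremental QALY and the cost-utility ICER are biased, and the bias can be material: the increment may be lost, inflated or reversed in sign. The share rests on the visit schedule, linear interpolation and the treatment of the first day. The QALY and dollar figures rest on assumed utilities and an assumed cost, and show what is possible rather than what is expected.

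This should be fixed, but its reach is limited. ED length of stay, the sample size, the effectiveness analyses and the cost-effectiveness analysis on ED time are untouched. Since all three EQ-5D-5L measurements are planned, nothing is lost if the rule is corrected before unblinding.

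**What to change.** Replace the QALY sentence with:

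> QALYs over 42 days will be calculated as the area under the curve (trapezoidal rule) of the EQ-5D-5L utilities at days 1, 7 and 42.

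Add one sentence on the interval from day 0 to day 1, labelled as an assumption because no day-0 EQ-5D-5L is collected. Carrying the day-1 value back is one option. It applies a utility measured after care to the period before and during care, but concerns only 1 day of 42.

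The change can go into the detailed analysis plan that the protocol foresees before unblinding, or into a health-economic plan fixed at the same stage. It needs no new questionnaires, visits or patients. The small cost is that each patient's QALY then needs all three utilities, so more patients will have a component missing; the multiple imputation already planned for the economic evaluation covers this.

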#### Process evaluation

A series of semistructured qualitative interviews will be undertaken to assist in the trial process evaluation. About 40 ED clinicians and 40 trial participants managed by primary-contact physiotherapists will be invited to participate. Clinicians will be purposively selected to vary by profession, age, gender and experience working in the ED. Trial participants will vary in gender, age, musculoskeletal condition, and triage category.

Only patients randomised to the primary-contact physiotherapy group will be verbally invited to participate in the qualitative interviews by their treating primary-contact physiotherapist during the ED visit. If participants agree, the primary-contact physiotherapist will provide a copy of the participation information sheet and will get participants’ consent to share their preferred contact details with the research team. The research team will then contact interested participants to explain the semistructured qualitative interview in more detail and gain informed verbal consent. Participants’ semistructured qualitative interviews will occur between days 1 and 42 following study randomisation.

The ED clinicians (physician and nurse practitioners, and physiotherapists) of each involved hospital ED will also be invited to participate in the semistructured qualitative interview. Clinicians will receive an invitation email from the head of department to take part in the trial qualitative interview and will be asked to read the participant information sheet and consent form attached in the email. Clinicians who agree to participate will be invited to register their interest via a REDCap link and contacted by the research team. Clinicians' semistructured qualitative interviews will occur after 50 patients are randomised at a participating hospital ED.

The interviews will be semistructured, audio-recorded and transcribed, and will follow the study procedures. The audio recordings will be stored in a password-protected University of Sydney drive and deidentified. The main aim of the interviews will be to qualitatively explore the implementation outcomes of acceptability and feasibility by examining clinicians’ experiences, opinions, barriers and facilitators, as well as patient’s experiences and overall satisfaction with the primary-contact physiotherapy care pathway.

## Ethics and dissemination

This trial protocol is in accordance with the principles of the Declaration of Helsinki. This study received ethical approval from the SLHD HREC (RPAH zone, protocol number X21-0143), Sydney, Australia, on 13 June 2023. A waiver of consent was granted by the SLHD HREC (RPAH zone) for patients to be enrolled in this trial. The obtained results will be submitted to peer-reviewed publications and will be presented at national and international conferences.

### Patient and public involvement

We have engaged with consumers and clinician-researchers from study conception. We sought feedback from emergency clinicians of the Sydney Local Health District and the RPA Green Light Institute for Emergency Care for the MRFF grant proposal and the study protocol. A consumer with lived experience sits on the trial steering committee and actively participate in meetings to provide ongoing feedback on trial conduct, reporting and interpretation.

### Trial status

Participant recruitment started on 22 November 2023, and the study is expected to be completed by June 2025.
